#### Secondary outcome measures

Secondary outcome measures include the following:

Changes from baseline in the average number of monthly headache days assessed during the 8-week follow-up period, specifically at two time windows: weeks 7–10 (Follow-up weeks 1–4) and weeks 11–14 (Follow-up weeks 5–8).

Changes from baseline in the average monthly acute medication use days (AMDs) during the treatment period and at follow-up time points. AMD is defined as the number of calendar days per month on which the participants used any acute migraine medication. AMD will be assessed at baseline, during the treatment period (weeks 3–6), and at follow-up time points (weeks 10 and 14).

The degree of pain will be evaluated using the visual analog scale (VAS).

The migraine-specific quality of life will be measured using the Migraine-Specific Quality of Life Questionnaire(MSQ) (28) from baseline to endpoints.

The headache symptom score will be evaluated based on the standards outlined in the “Guiding Principles for Clinical Research of New Chinese Medicines,” issued by the Ministry of Health in 2002, to assess various indicators.

### Safety monitoring and adverse event reporting

To maximize participant safety and proactively minimize risks, all participants will undergo a careful anamnesis and baseline assessment before the first treatment. During the study, the participants undergoing acupuncture treatment may experience adverse events (AEs), including but not limited to pain, subcutaneous congestion, hematoma, local infection, and, in rare cases, severe events such as syncope. Safety assessments will encompass vital sign measurements (blood pressure, heart rate, respiration rate, body temperature) and physical examinations. These vital sign measurements will be performed before the start of the protocol (at baseline assessment) and at key points during the treatment period (before and after treatment). Their primary purpose will be to monitor participant safety and ensure early detection of potential adverse reactions, rather than to serve as clinical indicators of acupuncture efficacy. Detailed documentation of AEs will include the time of occurrence, duration, classification, severity, remedial actions, and final resolution. Participants will be instructed to report any abnormal reactions or discomfort, which will be carefully documented, including the time, severity, and potential causes. Regardless of their relationship to the treatment, all AEs will be promptly and appropriately managed, recorded in the Case Report Forms (CRFs), and reported to the study director and the Ethics Committee of the Affiliated Hospital of Shandong University of Traditional Chinese Medicine.

Mild and moderate AEs will be managed symptomatically and monitored, while severe AEs, such as death, life-threatening disability, or hospitalization, will receive emergency treatment and will be reported to the Research Ethics Committee within 24 h, which will provide guidance on whether the trial should be terminated. To minimize the risk of severe adverse events, all practitioners have received specific training on recognizing and managing autonomic adverse responses to acupuncture, consistent with safety guidelines outlined in recent systematic reviews (29, 30).

### Sample size

The sample size was calculated using the PASS 11.0 software. Based on published literature (12), the number of migraine attack days was estimated as the outcome indicator for long-term efficacy observation. The number of migraine attack days in the acupuncture treatment group was reduced by 3.9 ± 3.0 days, while the number of migraine attack days in the sham acupuncture control group was reduced by 2.2 ± 3.2 days. The level of statistical significance was set at *α* = 0.05, and test efficacy was defined as (1-*β*) = 0.90. The ratio of the sample size between the treatment and control groups was set at 2:1, resulting in an estimated requirement of 107 participants in the treatment group and 54 in the control group. Considering potential dropout during the trial, with a predicted shedding rate of 10%, the initial number of participants was set at 120 in the treatment group and 60 in the control group, totaling 180 participants.

### Data management

All personnel involved in data management, including data collectors, data managers, and statisticians, will receive training to ensure adherence to the study’s data management protocols. Each participant’s CRF will be meticulously completed by the investigator based on the participant’s hospital records and original observation notes. Data entry will be conducted using the EpiData 3.1 software with a double-entry system by independent data entry personnel. The data manager, in collaboration with the principal investigator, will define the range and logical checks for the data and program these into the system to prevent errors. Any discrepancies found during data entry or validation will be documented and corrected, with records of the errors and corrections maintained.

All data, including paper CRFs and electronic files, will be securely stored. Paper records will be archived in a designated order and stored in a secure location, and electronic documents will be securely stored on a passwordprotected computer. These records will be preserved for at least 5 years following publication, in accordance with national regulations on clinical trial data management.

The Ethics Committee will periodically review the trial’s progress, monitoring data collection, allocation, and security. A formal data monitoring committee (DMC) will not be established. This decision is justified by the low-risk nature of the interventions (acupuncture and sham acupuncture) when performed by certified practitioners, the relatively short duration of the treatment phase (6 weeks), and the fact that no formal interim analyses for efficacy are planned. Instead, safety monitoring responsibilities will be jointly handled by the principal investigators and the Ethics Committee, which will conduct periodic reviews of safety data (including all AEs and SAEs) in addition to its standard oversight of trial conduct.

### Data analysis

Statistical analysis will be performed using SPSS 25.0 and the R software package. The primary analysis will be based on the full analysis set (FAS), which will include all participants who receive at least one acupuncture treatment and have primary outcome data. Missing baseline data for primary outcomes will lead to exclusion from the FAS. Sensitivity analysis will be conducted using the per-protocol set (PPS), comprising participants who meet all inclusion and exclusion criteria, have valid baseline data, demonstrate good compliance, and have not violated the study protocol. Safety analysis will be performed based on the safety set (SS), which will include all participants who receive at least one acupuncture treatment.

Descriptive statistics will be used to summarize demographic and baseline characteristics. Categorical data will be presented as counts (n) and percentages (%), with differences between the groups analyzed using the chi-squared test or Fisher’s exact test. Continuous variables will undergo normality testing. Normally distributed data will be expressed as mean±standard deviation ($\bar{X}$ ± S) and compared between the groups using independent samples *t*-tests. Non-normally distributed data will be presented as medians and interquartile ranges [M, (P25, P75)] and analyzed using the Mann–Whitney U test. Repeated measures data that meet the assumptions of normality, homogeneity of variance, and sphericity will be analyzed using repeated measures ANOVA, with corrections applied as necessary for violations of sphericity. To ensure the study’s scientific reliability and rigor, we will work to keep missing data under 20% and will use multiple imputation to handle missing data for the primary outcome.

Bang’s Blinding Index will be calculated for each group with 95% confidence intervals using the Wilson score method. Blinding will be considered successful if BI values are close to zero (|BI| < 0.3). Group differences in the CEQ scores will be compared using independent samples *t*-tests (or the Mann–Whitney U test if data are non-normally distributed). If the CEQ scores differ significantly between the groups, sensitivity analyses will include the CEQ as a covariate in primary outcome models (ANCOVA or mixed models) to adjust for potential expectancy effects. Correlation analyses will explore associations between the CEQ scores, acupuncture sensation scores, and primary outcomes to identify potential mediators of treatment effects.

Safety analysis will include the incidence of adverse events (AEs) during the study, with group comparisons of treatment-related adverse events conducted using a chi-squared test or Fisher’s exact test. Additional analyses may be conducted as deemed appropriate, with further details provided in the statistical analysis plan. Statistical significance will be set at a *p*-value of <0.05 for all analyses.

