### Outcome measures

#### Primary outcome measures

The primary outcome measure is the change from baseline in the average number of monthly headache days during weeks 3–6 of the 6-week treatment period.

According to the headache diary, patients will be asked about the duration of headache, defined as the number of days on which the headache lasted for at least 4 h. Headaches will be considered according to the ICHD-III criteria: criteria C and D (1.1) for migraine without aura, criteria B and C (1.2) for migraine with aura, or criteria 1.6 for possible migraines. Patients will also be required to record, on days with a migraine or headache, successful treatment with trastum, ergot, or other migraine-specific acute drugs.

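### The full analysis set requires observed primary outcome data, which conflicts with the promised multiple imputation and drops participants who leave before week 3

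*Protocol article*

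**What the plan says.** All the rules at issue stand in one section of the protocol article, Data analysis.

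- **Primary set.** The primary analysis uses the FAS, "which will include all participants who receive at least one acupuncture treatment and have primary outcome data".
- **Baseline.** "Missing baseline data for primary outcomes will lead to exclusion from the FAS".
- **Missing data.** The authors write that "we will work to keep missing data under 20% and will use multiple imputation to handle missing data for the primary outcome".
- **Other sets.** The per-protocol set (PPS) serves as a sensitivity analysis. It is limited to eligible participants with valid baseline data who complied well and did not breach the protocol. The safety set is for safety only. No wider efficacy set is named.

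Under Primary outcome measures, the outcome is the "change from baseline in the average number of monthly headache days during weeks 3–6 of the 6-week treatment period", taken from a headache diary. Under Sample size, a 10% dropout allowance raises the requirement from 107 + 54 to 120 + 60 participants.

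**The concern.** The primary outcome is a change score, so it needs a baseline value and a weeks 3–6 value. The FAS makes both a condition of entry. Imputation exists for participants who lack the second value, and these are the people the FAS has already removed. One rule cancels the other, at least for anyone with no diary data in the outcome window.

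Whether someone provides weeks 3–6 data is decided after randomisation and may depend on treatment. Real needling is deeper and requires Deqi, whereas sham needling is about 2 mm without manipulation. Participants may withdraw at any time. If early leaving differs by arm, or leavers fare differently from stayers, the randomised comparison is no longer protected. The PPS cannot show whether this matters, because it selects still more strongly on behaviour after randomisation.

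This is not detail left to a statistical analysis plan. The set definition and the imputation rule are both fixed here, and a later plan could follow one only by departing from the other.

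**Working it through.** **1. Who can be imputed under the stated rules?**

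| Participant (treated at least once) | In FAS? | Imputed? |
|---|---|---|
| Baseline and full weeks 3–6 diary | Yes | Not needed |
| Baseline and partial weeks 3–6 diary | Depends on what counts as having outcome data | Only if partial data count |
| Baseline, no weeks 3–6 diary (for example, left before week 3) | No | No |
| No baseline | No | No |

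On the strict reading imputation has no one to act on. On the generous reading it acts on row 2 only. Row 3 is excluded on either reading.

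**2. The plan's sample size.** Inputs from Sample size: reductions of 3.9 (SD 3.0) and 2.2 (SD 3.2), difference 1.7, alpha 0.05 (taken as two-sided, since one-sided does not reproduce the figure), power 0.90, ratio 2:1.

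- Control: (3.2² + 3.0²/2) × (1.960 + 1.282)² / 1.7² = 14.74 × 10.51 / 2.89 = 53.6, so 54. Treatment: 108. The plan states 54 and 107.
- Dropout: 107/0.9 = 118.9 and 54/0.9 = 60. The plan states 120 and 60.

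The sample size is reproduced and already allows for 10% loss. It is not in question.

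**3. How many could be affected?** Assume all loss occurs before the outcome window, equally by arm.

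- 10% loss: 0.10 × 180 = 18 (12 + 6).
- 20% loss: 0.20 × 180 = 36 (24 + 12).

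Both are upper bounds for their loss rate. The 10% covers dropout over the whole trial of 6 + 8 = 14 weeks, and anyone lost after week 6 already has the primary outcome. The 20% is a target ceiling for missing data.

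**4. How far could the estimate move?** Illustration only. Assume dropouts have zero change and completers change by the planning values. The completer difference is 3.9 − 2.2 = 1.70 days. The all-randomised difference is (1 − loss in acupuncture) × 3.9 − (1 − loss in sham) × 2.2.

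| Loss, acupuncture / sham | Number lost | All-randomised difference (days) |
|---|---|---|
| 10% / 10% | 12 + 6 = 18 | 3.51 − 1.98 = 1.53 |
| 20% / 10% | 24 + 6 = 30 | 3.12 − 1.98 = 1.14 |
| 10% / 20% | 12 + 12 = 24 | 3.51 − 1.76 = 1.75 |

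The completer figure overstates in the first two cases and slightly understates in the third.

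**The case against.** The strongest reply is that the outcome is built from four weeks of diary entries, not one visit. If having outcome data means having some entries, imputation can complete partial diaries and the two rules are compatible for those participants. That stands. A reader might infer that imputation has nothing at all to do, but this holds only on the literal reading. The reply does not help those with no weeks 3–6 entries.

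A second reply is that the illustration assumes informative dropout, which imputation under missing at random would not correct. Imputing within arm from baseline and observed diary weeks would return roughly 1.70 days unless those variables predicted the zero change. This also stands. It is why removing the FAS condition is not enough by itself.

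Three stronger readings are tempting, and the document does not support them:

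- **A known overstatement.** A reader might take 1.70 against 1.14 days (a ratio of 1.49) as the bias. It is one unfavourable scenario. Lack of benefit or suspicion of sham could equally raise loss in the control arm, where the sign reverses.
- **A loss of power caused by the FAS wording.** At 10% loss (108 + 54) power is 0.897, essentially as planned. Any shortfall at heavier loss comes from the absent data, and imputation does not restore that information.
- **Exclusion of the sham arm.** The FAS and safety set speak of acupuncture treatment only. But Study design refers to both real and sham treatment, and the safety analysis compares groups, so both arms are plainly meant. This is at most a clarification.

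Nor does the section present the PPS as its missing-data analysis, so it cannot be faulted for failing in that role.

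**Conclusion.** The point holds as a contradiction between two stated rules. As written, treated participants with no weeks 3–6 data leave the primary analysis because of a post-randomisation event, and the stated imputation cannot reach them. No efficacy analysis in the document retains them.

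At most 18 of 180 participants would be affected at 10% loss and 36 at 20%, if all loss precedes the outcome window. The size and direction of bias cannot be derived from the document. The range of 1.14 to 1.75 days against 1.70 rests on the assumptions of zero change in dropouts and planning-value change in completers. It shows only that loss by arm can matter relative to a 1.7-day planned effect.

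Recruitment is scheduled to continue until 31 December 2026, so the definition can still be settled before the data are analysed.

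**What to change.** - **Analysis set.** Delete the condition that primary outcome data be present. Define the FAS as all randomised participants, or all with at least one allocated session, real or sham, analysed in their allocated arm. Naming both kinds of session also clears up the wording, and the safety set can be worded the same way. Reconcile the sentence on missing baseline data with the definition chosen.
- **Imputation.** Apply the multiple imputation already promised to that set, using baseline and the observed diary weeks.
- **Sensitivity.** Because this imputation assumes data missing at random, add a delta-adjusted analysis in which imputed outcomes are made progressively worse. Keep the PPS as supportive.

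The cost is a few changed sentences and slightly more analysis work. No new data are needed and the sample size is unchanged.

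### Repeated secondary outcomes are assigned to complete-case repeated-measures ANOVA with no imputation; a prespecified mixed model on all observed windows would be better

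*Protocol article*

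**What the plan says.** The Data analysis section of the protocol article gives one rule for longitudinal data: "Repeated measures data that meet the assumptions of normality, homogeneity of variance, and sphericity will be analyzed using repeated measures ANOVA". The same sentence then makes provision for one of these conditions failing: "with corrections applied as necessary for violations of sphericity". For continuous variables in general it adds: "Non-normally distributed data will be presented as medians and interquartile ranges [M, (P25, P75)] and analyzed using the Mann–Whitney U test". On missing data it says: "we will work to keep missing data under 20% and will use multiple imputation to handle missing data for the primary outcome". No missing-data method is named for any other outcome.

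The Secondary outcome measures section defines the follow-up headache-day outcome as change from baseline, "specifically at two time windows: weeks 7–10 (Follow-up weeks 1–4) and weeks 11–14 (Follow-up weeks 5–8". For acute medication days it says: "AMD will be assessed at baseline, during the treatment period (weeks 3–6), and at follow-up time points (weeks 10 and 14". VAS has no stated time points, and MSQ is described only as running from baseline to endpoints.

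The primary outcome is a single window: "The primary outcome measure is the change from baseline in the average number of monthly headache days during weeks 3–6".

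Mixed models are mentioned once, as one option for a sensitivity analysis of the primary outcome if the credibility/expectancy scores differ between arms. Further detail is referred to a statistical analysis plan that is not shown.

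**The concern.** Standard repeated-measures ANOVA needs a full row per participant. Someone who supplies weeks 3–6 and 7–10 but misses weeks 11–14 is removed from that analysis altogether. The stated imputation does not reach the secondary outcomes, so nothing in the article prevents this.

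The choice of method is also conditional on the data. If sphericity fails, a correction keeps the ANOVA in use. If normality or homogeneity of variance fails, no method for repeated data is named. The only other stated route is a rank test, which ignores the repeated structure and does not estimate a difference in days.

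At stake is what the trial can say about persistence of effect and about acute medication use, the latter being part of the stated hypothesis. If participants who respond poorly leave, and do so at different rates in the two arms, completers no longer compare like with like.

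**Working it through.** **1. The plan's own figures.** The Sample size section gives reductions of 3.9 ± 3.0 and 2.2 ± 3.2 days, α = 0.05 (taken as two-sided), power 0.90 and 2:1 allocation.
- Sham: (3.2² + 3.0²/2) × (1.960 + 1.282)² / 1.7² = 14.74 × 10.51 / 2.89 ≈ 53.6, so 54; acupuncture 108. The protocol has 54 and 107. Welch power at 107/54 is 0.896.
- Dropout of 10%: 107/0.9 = 118.9, so 119; 54/0.9 = 60. The protocol has 120 and 60.

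These figures reproduce and rest on the single-window primary outcome. The present point does not touch them.

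**2. Participants lost to listwise deletion.** The only documented rate is the anticipated 10% dropout over the trial; rates per window are assumptions.
- Monotone dropout: listwise loss equals total dropout. At 10%, 180 × 0.90 = 162 are kept. At 20%, 180 × 0.80 = 144.
- Independent gaps at three windows: loss = 1 − (1 − p)³. For p = 5%, 1 − 0.857 = 14.3% (154 kept). For p = 10%, 1 − 0.729 = 27.1% (131 kept).
- If the headache-day ANOVA used only the two follow-up windows, the exponent is 2 and the losses are 9.75% and 19%. The same two figures give the further loss within the full analysis set, which already requires primary outcome data. The article does not say which windows enter the ANOVA.

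**3. Precision and bias.** A simulation with 3,000 runs per scenario used 120/60 participants and three windows. Mean changes were −3.9 and −2.2 in every window, so the true difference is −1.70. The SD was √((2 × 3.0² + 3.2²)/3) = 3.07. Correlations were assumed: 0.7 between adjacent windows and 0.5 between first and third. Dropout was monotone, after the first and second windows. The complete-case estimate uses the participants ANOVA would keep. The comparator is the likelihood estimate of a saturated mixed model, without baseline or centre terms. Results are for the last window:

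| Dropout | Nominal rate per step | Mean completers | Complete-case: mean (SE) | Mixed model: mean (SE) |
|---|---|---|---|---|
| Completely at random | 5% | 162 | −1.719 (0.510) | −1.715 (0.501) |
| Completely at random | 10% | 146 | −1.726 (0.545) | −1.725 (0.529) |
| Depends on earlier response, more so in sham | 5% | 150 | −1.057 (0.528) | −1.708 (0.529) |
| Depends on earlier response, more so in sham | 10% | 132 | −0.860 (0.578) | −1.707 (0.577) |

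When dropout is completely at random, both estimates stay within 0.03 days of the truth, and the complete-case SE is larger by 0.510/0.501 − 1 ≈ 2% and 0.545/0.529 − 1 ≈ 3%. In the response-dependent scenario the complete-case estimate is attenuated by 1 − 1.057/1.70 ≈ 38% and 1 − 0.860/1.70 ≈ 49%, and the mixed model is not. That scenario was made deliberately strong. It loses about 17% (30/180) and 27% (48/180) in total, more than the 10% anticipated, so it shows that bias can arise and is not a forecast.

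**The case against.** The strongest reply is that the plan is less rigid than it looks.

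- **Sphericity.** The plan corrects for violations, so a reader who infers that ANOVA is abandoned whenever any assumption fails goes too far. The gap is confined to normality and homogeneity of variance.
- **Targeting the windows.** A reader might infer that ANOVA cannot answer the questions posed for weeks 7–10 and 11–14. The article does not support that. ANOVA can supply contrasts at each window, and the general t-test or Mann–Whitney rule could be applied to each change score. Which contrast is reported may sit in the analysis plan that is not shown.
- **Size of the loss.** A reader might take 27% as the expected loss, or as a breach of the 20% target. It needs independent 10% gaps at each window. Monotone dropout at the documented 10% loses 10%, and the article does not say whether 20% applies per window or overall. Nor does it give dropout by period, so it cannot be said that dropout is highest in follow-up.
- **Remedy.** A mixed model does not cure everything. It still assumes roughly normal residuals, removes dropout bias only under missingness at random, and addresses the named windows only if arm-by-window contrasts are prespecified. Imputing the secondary outcomes would also deal with the missing windows.
- **Scope.** A reader might extend the point to MSQ and VAS, but the text gives no schedule for them that would show it.

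All of this stands and sets the limits of the point. It does not remove the core. ANOVA for repeated data is a stated choice and not a detail left open, and imputation is stated for one outcome only.

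**Conclusion.** The point holds for the repeated secondary outcomes whose time points are given: headache days at weeks 7–10 and 11–14, and acute medication days at weeks 3–6, 10 and 14. As written, their analysis drops anyone with a missing window, has no imputation, and has no repeated-measures alternative if normality or equal variance fails.

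The loss is about 10% if dropout is monotone at the anticipated rate, and 14% to 27% under assumed independent gaps of 5% to 10% at three windows. The precision cost is minor when data are missing completely at random. The reason to act is possible bias when leaving depends on earlier response. Its size cannot be known from the article, and its direction depends on who leaves which arm.

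This should be changed, but it is not a threat to the main result. The primary outcome is one window with its own imputation, and the sample size is unaffected.

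**What to change.** For these secondary outcomes, replace the conditional ANOVA with one prespecified mixed model for repeated measures using every observed window. Include arm, window, arm-by-window, baseline, baseline-by-window and centre, with an unstructured covariance. For headache days the windows are weeks 3–6, 7–10 and 11–14; for acute medication days, the three stated post-baseline time points. Report the adjusted between-arm difference with a 95% confidence interval at each named window, whatever a normality test shows. Apply the same model to MSQ and VAS only where they are measured repeatedly. State that it relies on missingness at random and approximately normal residuals.

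The cost is wording in the protocol or analysis plan, plus code. SPSS 25.0 and R, both already named, fit this model. No new data are needed, and with recruitment scheduled to 31 December 2026 the change can be fixed before analysis.

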### Randomization and allocation concealment

Participants in this study are strictly being screened according to the diagnostic, inclusion, and exclusion criteria. A random number list was generated using SPSS 25.0 software and converted into random number cards. Participants will be randomly allocated into two groups in a 2:1 ratio: 120 participants in the acupuncture treatment group and 60 of them in the control group. The allocation process will be kept confidential using sealed, opaque envelopes. The random number cards will be placed inside these envelopes, which will be numbered sequentially. The envelopes will be opened in the order in which the participants enter the study, and the participants will be assigned to their respective groups based on the number inside the envelope, ensuring a 2:1 allocation ratio between the groups.

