### Blinding

Due to the specific nature of acupuncture, it is not feasible to blind practitioners. Therefore, blinding will be implemented for the participants, evaluators, and statisticians. Practitioners adhere to strict confidentiality protocols to avoid disclosing group allocation to the participants and evaluators. Evaluators are responsible for collecting and analyzing the data unrelated to the treatment process and are not exposed to any information about group allocation throughout the study. Statisticians are solely responsible for data analysis and are not involved in the treatment process, thereby ensuring the objectivity and impartiality of the results.

To evaluate participant blinding integrity, Bang’s Blinding Index (BI) will be calculated at the completion of the treatment phase (17). After the final treatment session, the participants will be asked to guess their group allocation (real acupuncture, sham acupuncture, or unsure) and to rate their confidence in this guess.

The Credibility/Expectancy Questionnaire (CEQ) (18) will be administered after the first treatment session. Group differences in the CEQ scores will be examined to verify that expectancy was balanced between the groups.

After the completion of statistical analysis, the unblinding procedure will be initiated. Researchers responsible for unblinding will disclose group information to the data analysts as necessary to finalize comparisons and interpret the study results.

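### The Wilson interval does not directly fit Bang's index with an unsure answer, and the |BI| < 0.3 success rule ignores sign, arm and sampling error

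*Protocol article*

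**What the plan says.** The Blinding section of the protocol article states that participants will be "asked to guess their group allocation (real acupuncture, sham acupuncture, or unsure) and to rate their confidence in this guess". This is done once, after the last session: "Bang’s Blinding Index (BI) will be calculated at the completion of the treatment phase".

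The Data analysis section then fixes two things. The index "will be calculated for each group with 95% confidence intervals using the Wilson score method". The verdict is also fixed: "Blinding will be considered successful if BI values are close to zero (|BI| < 0.3").

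The article does not say how a Wilson interval is formed for an index built from three answers. The verdict is worded on the value of the index. It gives no role to the confidence interval or to the sign, and the two arms are treated alike. Planned arm sizes are "120 participants in the acupuncture treatment group and 60 of them in the control group".

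**The concern.** With an unsure category, Bang's index in one arm is a difference between two multinomial proportions and runs from -1 to 1. The Wilson score interval is a method for one binomial proportion. The two match only if nobody answers unsure, when the index reduces to 2p - 1. The trial offers that answer, so two analysts following the text could report different intervals.

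The success rule is a separate matter. The sign of the index means something different in each arm. A negative value in the sham arm means that more participants believed they had real acupuncture than guessed sham, which is what a convincing sham produces. A positive value in the acupuncture arm can reflect the same belief. A symmetric cut-off applied to each arm treats this pattern like unblinding once it reaches 0.3 in size, and accepts correct guessing in both arms as long as each value stays below 0.3.

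The verdict matters for interpretation. The primary outcome comes from a patient diary, practitioners are not blinded, and real and sham needling differ in site, depth and deqi. The Discussion gives the aim as showing specific effects beyond placebo, and a reader will lean on the blinding result to judge that.

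**Working it through.** **Inputs.** From the article: three answer categories (Blinding), planned arms of 120 and 60 (Randomization and allocation concealment), the Wilson interval and the 0.3 cut-off (Data analysis). The article gives no derivation of 0.3, so there is no figure of its own to reproduce. It gives no expected guess distribution either. The distributions below are assumptions, written correct/incorrect/unsure, and everyone is taken to answer.

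**Formula.** BI = pc - pi, Var(BI) = [pc + pi - (pc - pi)²]/n, 95% CI = BI ± 1.96 × SE.

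**Interval, one example.** n = 60, 30/20/50, so BI = 0.10. Var = (0.50 - 0.01)/60 = 0.00817, and SE = 0.0904.

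| Method | 95% interval | Width |
|---|---|---|
| Multinomial | -0.08 to 0.28 | 0.354 |
| Wilson on (BI + 1)/2, back-transformed (unsure counted as half) | -0.15 to 0.34 | 0.488 (38% wider) |
| Wilson on 0.10 as if it were a proportion | 0.05 to 0.20 | 0.155 (56% narrower) |
| Wilson among guessers, 2r - 1, scaled by the share who guess | -0.08 to 0.25 | 0.331 |

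**Interval, coverage** (100,000 simulated trials per scenario; nominal 95%):

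| Scenario | Multinomial | Guessers only, unscaled | Guessers, scaled | Unsure as half |
|---|---|---|---|---|
| n = 60, 20/60/20 | 94.1% | 89.9% | 94.3% | 97.1% |
| n = 120, 20/60/20 | 94.5% | 82.7% | 94.3% | 97.4% |
| n = 60, 25/25/50 | 94.3% | 94.7% | 94.7% | 99.5% |

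The named method can therefore give anything from near-nominal coverage to 83% or 99.5%, depending on a step the article leaves open.

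**Rule, convincing sham.** Suppose that in both arms 60% believe they had real acupuncture, 20% believe sham and 20% are unsure.
- The sham arm is then 20/60/20: BI = -0.40, SE = √(0.64/60) = 0.103, CI -0.60 to -0.20. The probability of |BI| < 0.3 is 0.148, so the arm is called a failure in about 85% of trials.
- The acupuncture arm is 60/20/20: BI = +0.40. At n = 120 the probability of passing is 0.079, so it fails in about 92%.

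**Rule, correct guessing in both arms.** Take 50/25/25 in each arm, so BI = +0.25.
- n = 60: SE = √(0.6875/60) = 0.107, CI 0.04 to 0.46.
- n = 120: SE = √(0.6875/120) = 0.0757, CI 0.10 to 0.40.

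Both intervals exclude 0, yet both values pass. At the evaluable sizes of 54 and 107 in the Sample size section, the nearest whole counts give 0.02 to 0.46 and 0.10 to 0.41, with the same conclusion. If +0.25 is the true value, an arm passes in 65% of trials (n = 60) and 73% (n = 120), and both pass together in 0.648 × 0.726 = 47%.

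**Side by side.** In the first case belief in real acupuncture is 60% in both arms, and the rule usually says failure. In the second it is 50% against 25%, and the observed values are called success.

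**The case against.** Five points can be made for the plan.

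- **The interval has no part in the verdict.** This stands. A reader might infer that the Wilson choice could change whether blinding is declared successful. It cannot, because the rule looks only at the value of the index. The interval issue affects reported precision only.
- **A workable Wilson version exists.** This also stands. Scaling the interval among guessers gives coverage of about 94% to 95%. So it goes too far to say that the planned interval must be wrong. The defect is that the named method does not apply directly and its adaptation is not given.
- **The 0.3 tolerance is a convention.** Partly right. Nothing in the article fixes another value, milder negative sham values pass, and pronounced unblinding is caught: at true BI +0.50 (65/15/20, n = 60) the rule passes only about 2% of trials. But this defends the size of the tolerance, not its symmetry or its silence on sampling error.
- **The guess is taken only at the end, when perceived benefit may drive it.** A reader might count this as a further flaw. The article gives the Credibility/Expectancy Questionnaire after the first session, compares it between arms and, if it differs, adjusts for it. An end-of-treatment guess also covers the whole course. The timing is a defensible choice.
- **A separate statistical analysis plan may say more.** Possibly, but the article names the interval and the cut-off outright, so these are stated choices and not omissions.

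**Conclusion.** The point holds on two counts.

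First, a single-proportion Wilson interval does not directly fit a three-answer index, and the consequence ranges from negligible to material according to the adaptation.

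Second, the symmetric rule can give a misleading blinding verdict in either direction. It rejects a convincing sham once the sham-arm index is -0.3 or lower, and accepts correct guessing in both arms below +0.3.

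The sizes rest on assumed guess distributions and full response. It would be too strong to say that the rule always fails a credible sham or always passes unblinding, since both statements depend on where the index falls relative to 0.3. Nor does the article support any effect on the trial's main result: the rule triggers no change to the primary analysis, analysis sets, sample size or alpha. What is at stake is how blinding is reported and how a positive result is read.

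**What to change.** - **Interval.** Replace the Wilson interval by a 95% interval from the index's multinomial variance, or a bootstrap, in each arm.
- **Reading.** Replace the |BI| < 0.3 pass/fail rule by a signed, joint reading of the two arms with their intervals. Positive values in both arms indicate unblinding. A negative sham value with a positive acupuncture value indicates that participants in both arms believed they had real acupuncture.

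A new hard cut-off is not a good substitute. For example, flagging the sham arm whenever its upper limit reaches +0.3 would flag a true index of 0 at n = 60 in about 9% (25/25/50), 20% (35/35/30) or 35% (50/50/0) of trials.

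The cost is a change of wording, best made before unblinding. No new data are needed, because the index and its interval can be computed from the guesses already being recorded.
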